### Data monitoring

2.15

Setting up a data monitoring committee and interim safety analysis are unnecessary because of the high security and short cycle of this trial.

### Harms

2.16

All adverse events thought to be related to the trial would be recorded rigorously and carefully. Any unexpected major serious complications suspected to be associated with ENGBD must be reported to interviewer and attending physicians, the trial may be temporarily stopped, and effective treatment measures in the first place will be taken by attending physicians.

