PTGBD has a technical success rate of nearly 97%, clinical response rates range from 56% to 100%,^[6]^ which is also associated with an overall adverse events rate as high as 14%, including bile leak peritonitis, cholecystitis, bleeding, subcapsular hematoma, pneumothorax, catheter misplacement, and inadvertent removal. Moreover, it is contraindicated in patients with large peritoneal ascites, coagulopathy, thrombocytopenia, and Chilaiditi syndrome.^[5]^ For these reasons, less-invasive forms of ENGBD that are more efficient, more safe and less painful have been developed.^[10]^ It was first proposed in 1984, but reported in 1990,^[11]^ the technical success, clinical success, post-procedure adverse events were 88.9%, 81.5%, 9.3%, respectively, according to the data provided by the only two randomized controlled studies^[9,12]^ in comparing ENGBD and EGBS. Despite such promising achievement from previous studies, the benefits of ENGBD and PTGBD on major clinical outcomes have never been compared prospectively. In particular, the effects of the two drainage method on LC remains uncertain and not only an extensive evaluation but also a retrospective study pointed out that ENGBD was more conducive to the smooth implementation of LC.^[13]^

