### Blinding

2.13

This is an open-label, unblinded trial for patients and physicians because of the nature of the intervention (position and shape of drainage tube). However, the investigator of collecting secondary outcomes, the assessor of clinical and biological data in charge of statistical analyses and outcome assessment will be masked as to the subjects assigned group.

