#### Collection, management

2.14.1

All data are prospectively collected and managed by the well-trained research volunteers.

The baseline data would be collected and registered on inclusion: age, sex, body mass index (BMI), body temperature, interval between onset of AC and drainage, comorbidities and coexisting conditions, american society of anesthesiologists (ASA) grade, charlson comorbidity index (CCI), AC grade based on TG 18 severity grading,^[4]^ white blood cell (WBC) count, electrolytes, total bilirubin, C-reactive protein (CRP), and so on. This would systematically reflect the characteristics of participants.

The peri-drainage data would be obtained from 2 hours before drainage to one week after ENGBD or PTGBD, such as drainage success, clinical remission, adverse events, pain scores within 2 hours before drainage and at post-drainage 24 h, 48 h, 72 h, etc.

The following data are collected and registered on peri-LC: gallbladder wall thickness changes (pre-drainage to pre-LC), duration and hemorrhage of LC, gallbladder integrity, drainage tube, hospitalization (hospital stay after gallbladder drainage and cholecystectomy), surgical site infection, severe adhesion, pathology, and LC-related complications.

Results that are negative or undetected or measured as 0 should have corresponding symbolic representation and can not be vacant, in order to distinguish from missing values. The treatment of outliers should be judged from both medical and statistical aspects by the statistician during blind examination.

Images and biological samples including venous blood and bile will be collected for probably ancillary and long-term research. Also, all patients will be followed up 6 months after cholecystectomy.

The volunteers of data acquisition have rich clinical experience and rigorous working attitude, and received training and guidance. Data storage would be carried out by two independent investigators to ensure reliability and validity.

We would also pay attention to and collect the information of the participants who discontinue or deviate before cholecystectomy and the follow-up are completed. To promote participants’ retention and enthusiasm, we would establish workflow manuals contact patients regularly, communicate properly and take effective care of their health.

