#### Analysis

2.14.2

A predefined statistical analysis plan will be followed. All statistical analyses were conducted with IBM SPSS (version 21.0). *P* values of <.05 were considered to represent statistical significance. Categorical variables would be reported as counts and percentages. The mean and standard deviation or median with interquartile ranges (IQR) were used to describe continuous variable data, as appropriate.

The primary analysis is a comparison between ENGBD and PTGBD for the pain remission based on an intention-to-treat principle. A multilevel, random-slope model would be fitted to the data with time points nested in patients to allow for clustering of data within each patient. This model adjusted for the fixed effects of treatment group, time (−2, 24, 48 , or 72 hours), and treatment × time interaction. An unstructured covariance pattern was selected for the repeated measurements as the least restrictive structure, which resulted in better model fit based on log-likelihood values than more constrained patterns. Estimates of the difference in pain scores between treatment groups were assessed overall and at individual time points.

The secondary analysis is a comparison between ENGBD and PTGBD for the rates of technical and clinical success, adverse events, and changes in the gallbladder wall thickness . Also, the outcomes during cholecystectomy including time duration, open conversion would also be analyzed. The Chi-square test or Fisher exact test was used for dichotomous variables, and Wilcoxon test was used for rank data. For quantitative data, two-tailed Student *t* test is used, if the normal distribution and homogeneous total variance are satisfying, otherwise, Wilcoxon test is used.

A blinded adjudication committee will assess the occurrence of the primary and secondary endpoints after the last patient has completed follow-up.

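### Section 2.16 makes suspected relatedness a condition for recording adverse events, names no judge and does not match section 2.14.1, which could distort the planned between-arm comparison

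*Protocol article*

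**What the plan says.** **Recording (2.16 Harms).** "All adverse events thought to be related to the trial would be recorded rigorously and carefully". No one is named to decide relatedness, and no blinding of that decision is stated.

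**Serious events (2.16 Harms).** "Any unexpected major serious complications suspected to be associated with ENGBD must be reported to interviewer and attending physicians". There is no matching sentence for PTGBD.

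**Collection (2.14.1).** The peri-drainage data run from 2 hours before drainage to one week after it and include items "such as drainage success, clinical remission, adverse events, pain scores within 2 hours before drainage" among others. No relatedness condition is attached. Surgical site infection and LC-related complications are listed separately as peri-LC data.

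**Analysis (2.14.2).** "The secondary analysis is a comparison between ENGBD and PTGBD for the rates of technical and clinical success, adverse events", among other outcomes. Also: "A blinded adjudication committee will assess the occurrence of the primary and secondary endpoints after the last patient has completed follow-up".

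**Blinding (2.13).** "This is an open-label, unblinded trial for patients and physicians because of the nature of the intervention". On allocation, the section then adds: "the investigator of collecting secondary outcomes, the assessor of clinical and biological data in charge of statistical analyses and outcome assessment will be masked".

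**Auditing (2.17).** An independent committee monitors the trial, including its safety, at least every 3 months.

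**The concern.** Relatedness is normally a property noted about an event once it has been recorded. Here it decides whether the event is recorded at all. That matters because adverse events are both a secondary objective (2.2) and a between-arm comparison (2.14.2), and the Introduction presents ENGBD as the safer option.

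The population makes the judgement hard. Section 2.6.1 enrols Grade II patients whose inflammation is not controlled by antibiotics and supportive care. It also enrols Grade III patients with jaundice, neurological or respiratory dysfunction, ASA-PS of 3 or more, or CCI of 4 or more. In such patients a respiratory deterioration or a recurrence of cholecystitis can be put down either to the illness or to the drainage. If that call leans one way for a new endoscopic technique and another way for the standard percutaneous one, the recorded rates differ even where the true rates do not. An analysis plan cannot restore events that never entered the data set.

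The ENGBD-only sentence adds an asymmetry of its own. It concerns reporting rather than the endpoint count, but it directs closer attention to one arm.

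**Working it through.** **1. The two recording rules side by side**

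| | 2.14.1 Collection | 2.16 Harms |
|---|---|---|
| Which events | Adverse events, no condition | Events believed related to the trial |
| Window | 2 h before to one week after drainage | None stated |
| Who judges relatedness | Not applicable | Not stated |
| Arms | Both | Recording: both; serious-event reporting: ENGBD only |

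Within the first week the rules differ. Between one week and the peri-LC period, 2.16 is the only rule in the text shown. That interval is not empty. Section 2.7 keeps the PTGBD catheter in for more than 2 weeks and the ENGBD tube for about 4 days, with cholecystectomy 3 months after drainage. Catheter time beyond the first week therefore falls mainly in the PTGBD arm. Table 1, which details the secondary outcomes, is not shown and might add a rule.

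**2. Who could be making the judgement**

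Section 2.13 masks the investigator collecting secondary outcomes. But 2.14.1 has research volunteers collect all data, 2.12 has volunteers open the allocation envelopes, and 2.7 has volunteers accompany patients to ERCP and PTGBD. The document does not separate these groups. So the masking in 2.13 does not clearly cover the relatedness judgement, nor does the text show that it fails to.

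**3. Sensitivity to one event**

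The plan gives no calculation for adverse events, so there is none to reproduce. Inputs: 11 per arm (2.10); for PTGBD "an overall adverse events rate as high as 14" per cent, and 9.3% for ENGBD (both Introduction).

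- Expected events, PTGBD: 11 × 0.14 = 1.54
- Expected events, ENGBD: 11 × 0.093 = 1.02
- Cited difference: 14 − 9.3 = 4.7 points
- Effect of one event on an arm: 1/11 = 9.1 points

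One unrecorded event outweighs the cited difference.

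**4. What unequal recording would do (assumed values)**

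Recorded rate = true rate × share of events recorded. Take a true rate of 14% in both arms; the shares are assumptions, since the document gives none.

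| Share recorded, arm A / arm B | Recorded rates | Ratio B/A | Expected events of 11 |
|---|---|---|---|
| 80% / 80% | 11.2% / 11.2% | 1.00 | 1.23 / 1.23 |
| 90% / 60% | 12.6% / 8.4% | 0.67 | 1.39 / 0.92 |
| 100% / 50% | 14.0% / 7.0% | 0.50 | 1.54 / 0.77 |

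The ratio depends only on the two shares. Equal filtering loses events but leaves the ratio unchanged; only unequal filtering distorts it.

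**5. Power with complete recording**

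Two-sided 5% test, normal approximation, 14% against 9.3%, 11 per arm. The mean rate is 0.1165.

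- z = (0.047 × √11 − 1.96 × √(2 × 0.1165 × 0.8835)) / √(0.14 × 0.86 + 0.093 × 0.907)
- z = (0.156 − 0.889) / 0.452 = −1.62
- Power ≈ 5%

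A formal test would be uninformative even with perfect capture. The safety result will in practice be read from the raw counts.

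**The case against.** Several stronger readings are tempting, and the document does not support them.

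- *Unblinded staff decide what is recorded.* Section 2.16 names no judge and 2.13 masks the collector of secondary outcomes. Section 2.6.3 says who performs ERCP and LC; it does not say who assesses harms, and it does not mention PTGBD. That treating physicians would judge first is plausible but unwritten.
- *Only related events are kept.* This is the natural sense of 2.16, but the word is not there, and 2.14.1 carries no such condition. The sections conflict; the text does not settle which governs.
- *The loss cannot be repaired.* The blinded committee is to assess whether endpoints occurred, and nothing limits it to events already recorded. The auditors also review safety. Whether either would search source records is not stated, so irreparability is unproven. Equally, no route to unrecorded events is described.
- *The 9.1 points measure the bias.* They do not. They equal 1/11, and any single chance event has the same effect. The 14% is also an upper figure, so 4.7 points is not a firm expectation.

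It can also be said that an article leaves safety forms and causality procedures to the full protocol, and that Table 1 may define the endpoint. That is fair for detail not given. It does not cover a rule the article does state, or its mismatch with another section.

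**Conclusion.** The point holds in a limited form. As written, 2.16 puts an unassigned relatedness judgement ahead of recording, states serious-event reporting for one arm only, and does not agree with 2.14.1. In an open-label trial that compares adverse-event rates between arms, this could bias the comparison if the judgement differs by arm. The documents do not show that it would, so no size of bias can be given. The ratios of 0.67 and 0.50 above rest on assumed recording shares.

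What can be stated is the sensitivity: about 1.0 to 1.5 expected events per arm on the cited rates, and 9.1 points for each event lost. The comparison has little power regardless, so the harm is to the descriptive safety account rather than to a decisive test. The primary pain outcome is not affected. The wording should be changed because the change is cheap and events not captured may not be recoverable.

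**What to change.** Reword 2.16 and reconcile it with 2.14.1:

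1. Record all adverse events in both arms, over the same stated window, whatever their suspected cause, with date and severity.
2. Hold relatedness as a separate field, assessed after recording, by a named role. Mask that assessment where feasible. Full masking will not always be possible, since some of the PTGBD events listed in the Introduction, such as pneumothorax or subcapsular hematoma, reveal the route.
3. Report all recorded events by arm, with the related ones shown separately.
4. State the reporting of unexpected serious complications for both arms.
5. Say whether the blinded committee works from recorded events alone or also from source records.

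The cost is a few sentences and a few more form entries for 22 patients. Reported event counts will be higher in both arms, and some will reflect the underlying illness; the relatedness field lets a reader separate these. For patients already enrolled, events left out under the current wording would have to be sought in source records, and the report should say how far that was done.

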### Auditing

2.17

A auditing committee consisting of an endoscopist, a surgeon and a sonographer, would monitor the trial at least once every 3 months. They remain independent from investigators and audit the frequency, procedures, and safety of the trial.

### Protocol amendments

2.18

Any changes to eligibility criteria, outcomes, and analyses would obtain approval from the ethics committee and the clinical trial.

### Confidentiality

2.19

Data would be handled in a confidential way. During the whole experiment, sensitive information such as the patient name, identity card number would not be exposed by coding.

### Access to data

2.20

All investigators would have access to the final trial data set after the end of the study.

### Dissemination policy

2.21

Data analysis, interpretation, and findings would be presented at academic conference and published in peer-reviewed journals. After the end of the trial, the interviewer will complete the writing and submit the manuscript via open access as soon as possible. Every participant would get the results and conclusions by mail.

## Discussion

3

To our knowledge, the study would be the first randomized controlled study powered to investigate the effect of ENGBD and PTGBD on peri-drainage and peri-LC in poor surgical AC population. Moderate and severe AC are usually associated with increased morbidity and mortality if rushed cholecystectomy is performed, it is becoming increasingly difficult to ignore the optimal management of AC, which includes transitional and permanent drainage, especially when it comes to critically ill patients with multiple comorbidities.

Only one small retrospective discovery of limited quality compared the ENGBD and PTGBD in AC patients to date.^[13]^ Part of the reason may be that ENGBD has to precisely over-select into the difficult visualizing, long, narrow, tortuous cystic ducts, which is a challenge because the ducts could be blocked by stones. The weighted pooled rates for technical success of ENGBD is 81% according to a proportion meta-analysis.^[8]^ However, this technique uses standard off-the-shelf ERCP accessories and can be performed in patients who are coagulopathic or using antiplatelet or anticoagulant agents, and it has certain advantages including better drainage effect which can be observed directly, convenient removal of drainage tube, no establishment of abnormal anatomic fistula, and so on. Thus, it may be regarded as a bridging therapy for acute cholecystitis followed by interval surgical cholecystectomy. Unfortunately, the impact of ENGBD on LC is rarely reported.

Compared to direct surgery, PTGBD shortens the operative duration of LC in patients with moderate to severe AC.^[21]^ However, it has a high risk of conversion to an open procedure during cholecystectomy by a multicenter analysis.^[22]^

As a large surgical endoscopy center that completes more than 2000 ERCPs per year, our team not only has a rich experience in cholecystectomy, but also masters excellently the endoscopic minimally invasive technique, we are confident to complete this major impact study. The trial has the potential to optimize drainage management with direct and realistic benefits for critical AC patients. It is worth mentioning that we would also pay attention to the effects of the two drainage methods on the cholecystectomy. If the study finds out that ENGBD may contribute to late cholecystectomy, it will be an excellent alternative or a powerful complement to PTGBD.

## Trial status

4

The current study protocol is version 3.0 (May 15, 2019). The trial opened to recruitment on October 10, 2018. Maybe we would complete the recruitment on October 10, 2020.
